#### Secondary outcome

Fidelity is defined as the degree to which the care unit has used the intervention guideline and implemented the intervention strategy as intended by the research team.^46^ To measure fidelity, a study-specific activity log will be used as recommended in previous research by Bunger *et al*.^47^

The research group will register for both arms those who attend digital introduction lectures presenting occupational safety and health for the healthcare sector and an introduction to the Swedish guideline on PHM, which is part of the intervention strategy for both arm A and B. Furthermore, the number of performed meetings with the implementation team at each care unit will be registered.

In addition, the activity log for arm A contains the five steps outlined in the intervention strategy: (1) the number of meetings and workshops carried out by the manager and implementation team, (2) the number of HCWs attending training modules, (3) the number of risk assessments with TilThermometer, (4) the percentage of fall risk assessments of all patients during the implementation period and (5) the performed SMET with active feedback through study completion. The evaluation of participating in workshops and digital and practical education will be evaluated using a questionnaire focusing on the usefulness of the content as well as how new knowledge on work environment and safe PHM can be applied in daily practice.

#### Implementation process evaluation

Information about the perceived usefulness of the use of strategies for safe PHM and barriers and facilitators that may influence the implementation process will be collected by inviting managers, implementation teams and HCWs at the care units to individual interviews or focus group discussions with employers and HCWs belonging to arm A. These will be held after the 4 month implementation period and before the 12-month follow-up. An interview guide will be developed for each target group of HCWs based on the consolidated framework for implementation research (CFIR) constructs.^48^

#### Contextual factors

Contextual factors will be collected from each participating care unit at baseline. These will include: the number of risk assessments the previous year; the number of managers and HCWs; the number of admissions of care recipients/places; the care burden; the number of inpatients; the amount of completed work environment training previous year; the current work environment policy; any completed training in PHM. During the whole study period, a number of explanatory and contextual factors will be collected to be able to explore the implementation process. Such factors could, for example, be organisational changes, understaffing, new managers and crises. These factors will be collected by the research team and the external facilitator in order to understand the implementation process and the outcomes of the implemented strategies in all care units. They will be collected from care units in both arm A and arm B, by the research group using field notes and conversations with managers.

### Data analysis and statistics

A power calculation was made to estimate the number of clusters and participants in each cluster. The Power calculation was based on the primary intervention effectiveness outcome NOSACQ-50, and a calculated minimum detectable change of 0.7 with an SD of 0.5 and within cluster correlation of 0.7. A power level of 0.8 (80%) and alpha of 0.05 was used. The calculation resulted in at least six care units (clusters) for each arm with a minimum of 15 participants in each care unit. Two predetermined conditions were taken into consideration in the randomisation, size of cluster and regional or municipal healthcare, as this ensured equal randomisation in arm A and arm B.

Quantitative data will be analysed using the IBM SPSS. Descriptive data are presented with mean and SD, median and range or counts and percentages. Comparisons between groups are analysed with an independent sample t test, Mann-Whitney U test or χ^2^ test. Multiple imputation will be used for missing data, and a sensitivity analysis will be made. Potential differences between the intervention arms regarding primary outcome at 4-month and 12-month follow-up will be estimated using linear mixed models for repeated measures. The models will be adjusted for possible confounders (baseline differences concerning age and working experience), and the results will be presented as point estimates with 95% CIs. Care units with a low rate of adherence to the assigned intervention strategy will in a subgroup analysis be compared with care units with high rate of adherence. The limit for statistical significance will be set at α=0.05. All interviews and focus group discussions will be digitally recorded and transcribed verbatim. The transcribed texts will be imported into NVivo V.12 (QSRInternational, Melbourne, Australia) to manage and code data. Qualitative content analysis will be used to analyse the data.^49^ A deductive approach will be used, and the implementation framework CFIR will guide the analysis in the first step.^50^ Thereafter, an inductive analysis will be used to describe the HCWs and the implementation of team members’ and managers’ experiences of the multifaceted intervention strategy for safe PHM with regard to the CFIR constructs in greater depth. Data from activity logs will be compiled and processed qualitatively and quantitatively.

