### Setting and participants

The study will be carried out in at least 12 healthcare units in regional and municipal healthcare centres in Sweden. At least six care units will receive the multifactorial intervention strategy (A) and at least six care units will receive the single intervention strategy (B). A care unit is defined as a unit with one manager responsible for all employees (HCWs) at the unit. A clinic or a nursing home with several smaller departments or care units will be included as one unit (cluster) to avoid contamination. We strive to recruit care units situated throughout Sweden to reach geographical spread.

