### Inclusion criteria

Regional healthcare: inpatient care units with a minimum of 15 HCWs employed at the unit.Municipal healthcare: nursing homes for older adults with a minimum of 15 HCWs employed at the unit.

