### Intervention effectiveness

#### Primary outcomes

The intervention effectiveness will be measured with regards to the safety climate using NOSACQ-50. This comprises 50 items across seven safety climate dimensions in the workplace (management safety priority, commitment and competence; management safety empowerment; management safety justice; workers’ safety commitment; workers’ safety priority and risk non-acceptance; safety communication, learning and trust in coworkers’ safety competence and trust in the efficacy of safety systems).^32^ The questionnaires are scored on a scale of 1–4, where 1 equals ‘strongly disagree’ and 4 ‘strongly agree’, where a score greater than 3.30 indicates a good safety climate. An additional 14 specific research-based questions to evaluate the safety climate for PHM will also be used in line with previous studies.^6^ These questions involve the dimensions of using equipment, other aspects of safety, performing risk assessment and coproduction between caregivers and patients. They also use a scale of 1–4, where 1 is ‘strongly disagree’ and 4 is ‘strongly agree’, based on the design in NOSACQ-50.^32^

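### At the stated minimum of six clusters per arm, 80% power holds only under a normal approximation; on 10 degrees of freedom, power for a 0.7-point difference is about 73%

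*Protocol article*

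**What the plan says.** The sample size paragraph under Data analysis and statistics in the protocol article bases the calculation on NOSACQ-50, the primary effectiveness outcome. Its inputs are "a calculated minimum detectable change of 0.7 with an SD of 0.5 and within cluster correlation of 0.7". It adds "A power level of 0.8 (80%) and alpha of 0.05 was used". The result is given as "The calculation resulted in at least six care units (clusters) for each arm with a minimum of 15 participants in each care unit". The Abstract and Setting and participants repeat the total of at least 12 units, at least six in each arm. The paragraph does not name the formula, say whether the test is one- or two-sided, or mention an allowance for the small number of clusters. The planned analysis, in the same section, is a linear mixed model for repeated measures, reported as point estimates with 95% confidence intervals.

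**The concern.** Whole care units are allocated to the strategies, so the evidence on the difference between arms comes from variation between units. With six units per arm, that variation is estimated on only 10 degrees of freedom, and the two-sided 5% critical value is 2.228 rather than 1.960. A normal approximation ignores this, and the effect is not negligible with 12 clusters. If six per arm was derived that way, the stated power and the stated alpha cannot both hold at the minimum size. Keeping alpha at 0.05 lowers power below 80%. Keeping the 1.960 cut-off raises the type I error above 5%. At stake is whether readers are given the right chance of missing the planned effect, and whether those running the trial know what the minimum number of units delivers.

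**Working it through.** **Inputs** (protocol article, Data analysis and statistics): difference 0.7, SD 0.5, within-cluster correlation 0.7 (read as the intracluster correlation), 15 participants per cluster, alpha 0.05, power 0.80, six clusters per arm. Two-sided testing is an assumption, taken from the planned 95% confidence intervals.

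**1. Reproducing the protocol's figure (normal approximation)**

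- Design effect = 1 + (15 − 1) × 0.7 = 10.8.
- Participants per arm without clustering = 2 × [0.5 × (1.960 + 0.842) / 0.7]² = 8.01.
- Clusters per arm = 8.01 × 10.8 / 15 = 5.77, rounded up to 6.
- Standard error of the arm difference at six per arm = 0.5 × √(2 × 10.8 / 90) = 0.245.
- Standardised difference = 0.7 / 0.245 = 2.858.
- Power = Φ(2.858 − 1.960) = 81.5%.

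The stated six per arm follows from this formula.

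**2. The same inputs on the degrees of freedom available**

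The variance of a cluster mean is 0.25 × (0.7 + 0.3/15) = 0.18, so the standard error is √(2 × 0.18 / k) for k clusters per arm. Power comes from the noncentral t distribution with 2(k − 1) degrees of freedom, two-sided alpha 0.05.

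| Clusters per arm | df | 0.7 / SE | Power (t) | Power (normal) |
|---|---|---|---|---|
| 5 | 8 | 2.609 | 62.9% | 74.2% |
| 6 | 10 | 2.858 | 73.1% | 81.5% |
| 7 | 12 | 3.087 | 80.9% | 87.0% |
| 8 | 14 | 3.300 | 86.6% | 91.0% |

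Simulated t tests on cluster means at six per arm (200,000 replicates) also give 73.1%. The difference detectable with 80% power at six per arm is 0.76 on 10 df, against 0.69 by the normal formula. Applying the 1.960 cut-off on 10 df would put the two-sided type I error at about 7.8%.

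**3. Can larger units make up the loss?**

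With six clusters per arm and correlation 0.7, power on 10 df is 72.5% with 10 participants per unit, 73.7% with 30, 74.1% with 100 and 74.3% with 1000. Of the cluster-mean variance of 0.18, 0.25 × 0.7 = 0.175 remains however many staff respond. Only more clusters, or a smaller between-unit variance, raise power appreciably.

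**4. Sensitivity to what the protocol leaves open**

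- One-sided alpha 0.05 on 10 df: 84.4%.
- Intracluster correlation: 80% power for 0.70 on 10 df is reached at about 0.58 or lower.
- Baseline adjustment: reaching 80% at 0.70 requires the variance to shrink by the factor (0.70 / 0.762)² = 0.844. Setting 1 − r² = 0.844 gives r ≈ 0.39 for the correlation between baseline and follow-up cluster means, with 10 df retained. The protocol states no such correlation.
- Covariates that use up cluster-level degrees of freedom work the other way if they explain nothing: 70.7% on 8 df.

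**The case against.** Several points on the other side limit the finding.

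- **Six is a floor.** The protocol says at least six per arm, and under Procedure all recruited units willing to take part are randomised. A reader might infer that the trial as run will be underpowered. The document does not support that: seven per arm already reaches 80%, and the shortfall applies only at the minimum.
- **The planned analysis is richer than the calculation.** NOSACQ-50 is measured at baseline, 4 months and 12 months and analysed with a repeated-measures mixed model after stratified randomisation. A moderate baseline correlation could recover the lost power. This stands, and 73% should not be presented as the power of the planned model. But the protocol's own 80% takes no credit for adjustment either, so like is compared with like.
- **Sidedness is not stated.** A one-sided test would clear 80%, but the 95% confidence intervals point to a two-sided test.
- **The inputs do give six.** They do, so this is an omitted small-sample allowance, not a slip in the sums.

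Three stronger readings are tempting and should be set aside:

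- **A ceiling on the scale.** Under Primary outcomes, "The questionnaires are scored on a scale of 1–4" and "a score greater than 3.30 indicates a good safety climate". Since 4.00 − 3.30 = 0.70, a reader might infer that the target is unattainable. It is attainable even if arm B ends exactly at 3.30, and no baseline or expected mean is given. The comparison shows only that 0.7 (1.4 SD) is large.
- **A mislabelled target.** The protocol already calls 0.7 a minimum detectable change and nowhere claims it is the smallest worthwhile difference.
- **A null result read as equivalence.** Nothing in the protocol plans this, and it commits to interval estimates.

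**Conclusion.** The point holds in a limited form. On the protocol's own inputs, six clusters per arm give 80% power only if the small number of clusters is ignored. Allowing for 10 degrees of freedom, power at that minimum is about 73% for a difference of 0.70, so the chance of missing the planned effect is about 27% rather than 20%.

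This rests on a two-sided test at alpha 0.05, exactly six clusters per arm with 15 participants each, the stated correlation of 0.7, and no credit for baseline or repeated measures. A change in any of these that raises power enough would restore 80%, but the protocol states none. The design and planned analysis are not invalid. The defect is a power statement that is too favourable at the size it describes.

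**What to change.** Replace the power statement under Data analysis and statistics with wording such as: *At the minimum of six clusters per arm with 15 participants each, power is about 73% for a difference of 0.70 (80% for 0.76), assuming SD 0.5, within-cluster correlation 0.7, two-sided alpha 0.05 and a t distribution with 10 degrees of freedom, without credit for baseline or repeated-measures adjustment.*

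If credit for adjustment is intended, show that calculation, with the assumed correlation and the degrees of freedom left after cluster-level covariates. In either case, update the figure to the number of clusters actually randomised; seven per arm would support about 81%.

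The cost is a change of wording and a slightly less favourable stated power. No extra units are required, and randomisation, data collection and analysis are unchanged.

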### Procedure

As a first step, the manager will sign an informed written consent form before the care unit’s participation in the study. All recruited care units willing to participate will be simultaneously randomised to either arm A or arm B by a computer-generated randomisation list. Stratification will be made in blocks by the size of the unit (large or small) and type of organisation (regional or municipal healthcare). Furthermore, care units in the same municipality and within the same regional healthcare departments will also be a factor in the stratification. The randomisation will be performed by an independent statistician prior to the baseline measurement in order to be able to adjust the planning and information to the care units belonging to arm A or arm B. The recruitment of care units and the randomisation into two intervention strategies (A and B) are presented in figure 1. The 12-month study period starts February 2023 and is divided in two phases. The first 4 month is classified as the active implementation period. In the following 8 months, the care units will continue to apply the intervention strategy.

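### The tests named for comparing groups assume independent healthcare workers although care units are randomised, and no care-unit effect is stated for any outcome analysis

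*Protocol article*

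**What the plan says.** Four statements in the protocol article bear on this.

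- **Unit of randomisation.** Under Procedure: "All recruited care units willing to participate will be simultaneously randomised to either arm A or arm B". Under Setting and participants the cluster is defined further: "A clinic or a nursing home with several smaller departments or care units will be included as one unit (cluster) to avoid contamination".
- **Sample size.** Under Data analysis and statistics the inputs for NOSACQ-50 are "a calculated minimum detectable change of 0.7 with an SD of 0.5 and within cluster correlation of 0.7". Power is set at 80% and the significance level at 5%. The result is given as "at least six care units (clusters) for each arm with a minimum of 15 participants in each care unit".
- **Group comparisons.** The same section states: "Comparisons between groups are analysed with an independent sample t test, Mann-Whitney U test", with a chi-square test as the third option. The sentence comes after the one on descriptive data, but it is not confined to baseline or to description.
- **Primary outcome.** Differences between the arms at 4 and 12 months "will be estimated using linear mixed models for repeated measures", adjusted for age and working experience.

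Nowhere does the article name a care-unit random effect, a cluster-robust variance, a cluster-level summary or any other allowance for clustering in the analysis. Table 1 lists many secondary effectiveness outcomes (SMET, global health, work strain, work ability, sickness absence, musculoskeletal disorders and others). No method is assigned to them by name.

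**The concern.** Healthcare workers in one unit share a manager, patients, equipment and routines, so their answers are correlated, and the sample size calculation says as much. The t, Mann-Whitney and chi-square tests treat each worker as a separate piece of evidence. Applied to individual responses in a cluster-randomised trial, they give standard errors that are too small, intervals that are too narrow and p-values that do not hold their level. With about 12 clusters, ordinary differences between units could be reported as effects of the multifactorial strategy.

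A mixed model does not remove the problem by itself. If its only random structure links the repeated answers of one person, the between-unit variation is still left out.

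**Working it through.** **Inputs.** From Data analysis and statistics: difference 0.7, SD 0.5, within-cluster correlation (ICC) 0.7, power 0.80, alpha 0.05, six clusters per arm, 15 participants per cluster. The article does not say whether alpha is two-sided; two-sided is assumed. It gives no ICC for the secondary outcomes, so 0.01 to 0.20 is an assumed range.

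**1. The plan's own figure.**
- Individuals per arm without clustering: 2 × [0.5 × (1.960 + 0.842) / 0.7]² = 8.01.
- Design effect: DE = 1 + (15 − 1) × 0.7 = 10.8.
- Clusters per arm: 8.01 × 10.8 / 15 = 5.77, rounded up to 6.

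The stated six clusters are reproduced, but only with the design effect. Without it about 8 individuals per arm would do. A one-sided alpha gives 4.54, hence 5 clusters, so two-sided is the reading that fits.

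**2. Type I error of a test that ignores the cluster.** With DE = 1 + 14 × ICC, the standard error is too small by the factor √DE, and the true two-sided error of a nominal 5% test is about 2 × [1 − Φ(1.96 / √DE)]. The last two columns are simulations of 6 + 6 clusters of 15 with no true difference (20,000 runs each).

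| ICC | DE | √DE | Error, formula | Individual-level t test, simulated | t test on cluster means, simulated |
|---|---|---|---|---|---|
| 0.01 (assumed) | 1.14 | 1.07 | 6.6% | 6.5% | 5.0% |
| 0.05 (assumed) | 1.70 | 1.30 | 13.3% | 13.6% | 5.1% |
| 0.10 (assumed) | 2.40 | 1.55 | 20.6% | 20.7% | 4.8% |
| 0.20 (assumed) | 3.80 | 1.95 | 31.5% | 31.8% | 4.8% |
| 0.70 (plan, NOSACQ-50) | 10.80 | 3.29 | 55.1% | 57.2% | 4.8% |

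The Mann-Whitney test at ICC 0.70 gave 54.5% in 2,000 runs. Fifteen is the plan's minimum per unit; larger units raise DE and make the error worse.

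**3. A mixed model with a person effect only.** This was simulated through its balanced equivalent, a comparison of person means over two follow-ups. The within-cluster variance was split 60/40 between person and residual, which is an assumption. The error is about 15% at ICC 0.05, 24% at 0.10 and 59% at 0.70. This applies only if no care-unit effect is fitted.

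**4. Power of a valid analysis.** Under the plan's inputs the variance of a cluster mean is 0.25 × 10.8 / 15 = 0.18. The standard error of the arm difference is √(2 × 0.18 / 6) = 0.245, and 0.7 / 0.245 = 2.86.
- Normal approximation: Φ(2.86 − 1.96) = 0.815.
- t test on 12 cluster means (10 degrees of freedom, noncentral t): 0.73.
- Seven clusters per arm (12 degrees of freedom): 0.81.

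**The case against.** The strongest reply is that a reader might infer that the whole trial will be analysed as if individuals had been randomised, and the article does not support that.

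- For the primary outcome it names a linear mixed model, which can carry a care-unit random effect. The reference to repeated measures names a model family and is not a full list of random effects. Age and working experience are fixed covariates, so the absence of care unit beside them proves nothing about the random part. The detail may sit in a full protocol or analysis plan that is not shown. This stands: for the primary outcome the problem is conditional.
- Table 1 places acceptability, appropriateness and feasibility under the primary outcome, so the mixed model may cover them too. That is also fair.
- The sentence on simple tests follows the one on descriptive data and may be meant for baseline comparisons. The wording does not limit it that way. If that was the intent, no between-arm method is stated for the secondary outcomes. It is therefore an inference, not a stated fact, that all secondary outcomes will be tested this way, but no other stated between-arm method could apply to them.
- The 55% figure pairs a simple test with a correlation given for NOSACQ-50, an outcome assigned to the mixed model. It should not be read as the error rate for the secondary outcomes.
- Clustering is not overlooked in the design: the sample size uses it, and the cluster is clearly defined.

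**Conclusion.** The sentence on group comparisons is wrong as written. It prescribes tests for independent observations in a trial that randomises care units and whose sample size reproduces only with a design effect of 10.8. An unseen analysis plan that handled clustering correctly would have to depart from this sentence for any outcome comparison it governs.

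For outcomes tested this way, the true error of a nominal 5% test is about 13% to 31% over assumed ICCs of 0.05 to 0.20, with clusters of 15 and six per arm. At an ICC of 0.01 the inflation is slight (about 6.5%). The 55% figure holds only if the plan's 0.7 applied to an outcome tested in this way.

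For the primary outcome, the model description leaves the care-unit effect unstated. That needs to be settled, but it does not show that the primary analysis ignores clustering.

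**What to change.** In Data analysis and statistics:

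1. Limit the t, Mann-Whitney and chi-square tests to description.
2. State that all between-arm outcome comparisons, primary and secondary, use models suited to the outcome type with a random intercept for the randomised cluster, as defined under Setting and participants, and with healthcare worker nested within cluster for repeated measures.
3. Name a small-sample degrees-of-freedom correction, such as Kenward-Roger or Satterthwaite for the linear models, because only about 12 clusters are planned. A t test on cluster means (10 degrees of freedom with 12 clusters) is a valid fallback.

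The cost is mostly wording, but not only that. Intervals become wider. With six units per arm, a cluster-level t analysis has power of about 0.73 under the plan's own assumptions instead of the stated 0.80, and the protocol should report this. Seven units per arm would give about 0.81, and because the article sets six as a minimum, more units are already allowed.

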## Aims and hypothesis

The overall aim of the proposed study is to evaluate the implementation and the effectiveness of a multifactorial intervention strategy for safe PHM (A) and compare it with a single intervention strategy (B). The specific aims are as follows: (1) to evaluate and compare the intervention effectiveness of the applied strategies regarding safety climate in relation to PHM, (2) to evaluate the implementation outcome concerning the HCWs’ perceptions of acceptability, appropriateness and feasibility of the intervention and (3) to explore the implementation process and fidelity to the interventions. The implementation process evaluation includes the HCWs’ experiences of the multifactorial intervention strategy for safe PHM. The hypothesis in this study is that care units receiving the multifactorial intervention strategy will develop a better safety climate in relation to PHM compared with care units receiving the single intervention strategy. Furthermore, the hypothesis is that the multifactorial intervention strategy will be perceived as more acceptable, appropriate and feasible than the single intervention strategy.

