### Outcome measures

A mix of quantitative and qualitative methods will be used as suggested when evaluating complex interventions.^25^ The data collection will start 2023 and be based on questionnaires, interviews and field notes of contextual factors, presented in table 1.

**Table 1 T1:** Presentation of outcome measures, method of data collection, data source and time points

Measure	Method of data collection	Data source	Time point
Primary outcome			
1. Intervention effectiveness			
Safety climate	Questionnaire (NOSACQ-50)	HCWs and managers	T0, T1 and T2
Safety for patient handling and movement	Questionnaire (research specific)	HCWs and managers	T0, T1 and T2
2. Implementation outcome			
Acceptability	Questionnaire (AIM)	HCWs and managers	T1 and T2
Appropriateness	Questionnaire (IAM)	HCWs and managers	T1 and T2
Feasibility	Questionnaire (FIM)	HCWs and managers	T1 and T2
Secondary outcome			
1. Intervention effectiveness			
Evaluation of the work environment	Questionnaire (SMET)	HCWs and managers	T0, T1 and T2
Global Health	Questionnaire	HCWs and managers	T0, T1 and T2
Work Strain	Questionnaire (Borg-CR 10)	HCWs and managers	T0, T1 and T2
Work performance—work ability	Questionnaire (WAI)	HCWs and managers	T0, T1 and T2
Perceived work environment Production loss Sickness presence Sickness influence on ability to work	Questionnaire	HCWs and managers	T0, T1 and T2
Sickness absence	Questionnaire	HCWs and managers	T0, T1 and T2
Work related musculoskeletal disorders	Questionnaire	HCWs and managers	T0, T1 and T2
Fit for work—physical strength	Questionnaire (single item)	HCWs and managers	T0, T1 and T2
Physical activity Daily physical activity Physical exercise the last 12 months Strenuous physical activity Time of daily physical activity	Questionnaire	HCWs and managers	T0, T1 and T2
2. Implementation outcome			
Fidelity	Observation, meeting notes, work documents, activity logs	Implementation team, external facilitator, research group	During implementation period of 4 months
Experiences of the intervention strategy and implementation process	Meeting notes, activity logs	Managers and implementation team members, external facilitator HCWs	Between T1 and T2
Experiences of the intervention strategy and implementation process (barriers and facilitators)	Interviews: focus group and individual. CFIR will guide the analysis.	Managers and implementation team members, HCWs	Between T1 and T2

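### The primary model names age and working experience as adjustments but not the baseline NOSACQ-50 score, and calling it a repeated-measures model does not make the follow-up contrast conditional on that score

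*Protocol article*

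**What the plan says.** All the places are in the protocol article.

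- **Analysis target** (Data analysis and statistics): "Potential differences between the intervention arms regarding primary outcome at 4-month and 12-month follow-up will be estimated using linear mixed models for repeated measures".
- **Adjustments** (next sentence): "The models will be adjusted for possible confounders (baseline differences concerning age and working experience". No other covariate is named.
- **Measurement** (Outcome measures, Table 1): the row reads "Safety climate Questionnaire (NOSACQ-50) HCWs and managers T0, T1 and T2". The baseline value of the primary effectiveness outcome is therefore collected in both arms.
- **Sample size** (Data analysis and statistics): it rests on "a calculated minimum detectable change of 0.7 with an SD of 0.5 and within cluster correlation of 0.7". It arrives at six or more care units per arm with at least 15 participants in each.
- **Hypothesis** (Aims and hypothesis): arm A units "will develop a better safety climate in relation to PHM compared with care units receiving the single intervention strategy".
- **Procedure**: units are randomised before the baseline measurement. The cohort is open, so workers hired later can join and will have no T0 answer of their own.

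**The concern.** The analysis sentence fixes a target, arm differences at two follow-up times, and the next sentence fixes a covariate list. The obvious prognostic variable, the unit's starting safety climate, is not in the list.

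The repeated-measures label does not settle how T0 is used:

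- If T0 is not one of the outcome rows, it is unused.
- If it is one, an unconstrained arm-by-time model gives either the raw follow-up difference or the difference in change. Neither is conditional on T0.
- Conditioning needs either T0 as a covariate or a constraint that both arms share one T0 mean. The article states neither.

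The choice carries weight in this trial because there are only 12 units and the plan assumes that most of the score variance lies between units. A chance difference in starting climate can then be sizeable relative to the target. If the estimator is left open, it could also be picked after the T0 imbalance has been seen.

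**Working it through.** **Inputs.** From Data analysis and statistics: difference 0.7, SD 0.5, within-cluster correlation 0.7, 15 per unit, 6 units per arm, 80% power, alpha 0.05. Assumed: two-sided testing, equal unit sizes, no loss, SD 0.5 as the SD of a score at one time, and r (the T0-to-follow-up correlation of unit means) from 0 to 0.7. The article gives no value for r.

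**1. The plan's own figure.** Individuals per arm without clustering: 2 × [0.5 × (1.960 + 0.842)/0.7]² = 8.01. Design effect: 1 + 14 × 0.7 = 10.8. Inflated: 8.01 × 10.8 = 86.5 per arm, and 86.5/15 = 5.77, so 6 units. This reproduces the stated number as a plain comparison of two means with no baseline term. Power at 6 units per arm is 81.5% by the normal approximation.

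**2. Size of a chance T0 difference.** Variance of a unit mean: 0.25 × (0.7 + 0.3/15) = 0.18. SE of an arm difference: √(2 × 0.18/6) = 0.245, and 0.245/0.7 = 35% of the target. A chance T0 difference exceeds 0.35 (half the target) in absolute value with probability about 15%. This treats allocation as simple and ignores any balance gained from stratification.

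**3. Carry-over if T0 is ignored.** A one-SE imbalance at T0 shifts the follow-up difference by r × 0.245, which is 0.07, 0.12 and 0.17 at r = 0.3, 0.5 and 0.7.

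**4. Power for 0.7 under three estimators.** All use a t reference, so that they can be compared with each other.

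- Follow-up only: SE 0.245, 10 df.
- Change score: SE 0.245 × √[2(1 − r)] = 0.290, 0.245, 0.190 at r = 0.3, 0.5, 0.7, with 10 df.
- Adjusted for the T0 unit mean: simulated 12-unit trials, 9 df. The formula 0.245 × √(1 − r²) gives 0.234, 0.212, 0.175, but it omits the cost of estimating the slope from 12 units. The simulated SD of the estimate is 0.248, 0.225, 0.185.

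| r | Follow-up only | Change score | T0-adjusted | Adjusted minus follow-up only |
|---|---|---|---|---|
| 0 | 73% | 45% | 68% | −5 points |
| 0.3 | 73% | 59% | 72% | −1 to −2 points |
| 0.5 | 73% | 73% | 79% | +6 points |
| 0.7 | 73% | 91% | 92% | +19 points |

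The table should be read along rows. Comparing a figure in one row with a figure in another mixes the choice of estimator with the unknown r.

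**The case against.** **The documents may not contradict themselves.** A reader might infer that the hypothesis and the power calculation concern a change over time while the analysis concerns a difference at follow-up. The text does not establish this. The hypothesis is worded as a comparison between arms, minimum detectable change is ordinary sample-size language, and step 1 reproduces the six units as a two-mean comparison. The wording is loose rather than contradictory. This objection stands.

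**T0 may already be in the model.** With T0, T1 and T2 all measured, T0 could be one of the repeated values, and a difference-in-change contrast would subtract a T0 imbalance. At r = 0.7 that is nearly as good as adjustment (91% against 92%). The article leaves this open, so any loss is conditional. Neither unconstrained contrast is T0-adjusted, however, and at r = 0.3 the change score is the worst of the three.

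**Baseline handling is often left to an analysis plan, and the list is headed as confounders.** That is fair as to detail. But the article does commit to a target and a covariate list, and the improvement is to that stated list.

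**The gain depends on an unknown r.** This stands too. At low r, adjustment loses slightly. A reader might argue that the within-cluster correlation of 0.7 makes a high r likely. It does not: that figure describes how alike workers in one unit are, not how stable unit means are over 4 or 12 months.

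**The SD may be that of a change.** The article does not say. If so, change-score power would be 73% whatever r is.

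**Stratification may reduce imbalance.** Unit size, organisation type and shared municipality or department are used in allocation. They do not target starting climate directly, but the 0.245 could be somewhat high.

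**Conclusion.** The point holds as a worthwhile improvement to a stated analysis. The primary contrast is set at follow-up, the T0 score is collected but not a named adjustment, and the repeated-measures model does not by itself condition on it.

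The unadjusted estimate is not biased. What is at stake is conditional imbalance, with an SE of 0.245 against a target of 0.7, and precision that could be had from data already collected. Compared with follow-up only, adjustment changes power by about −5 points at r = 0, −1 to −2 at 0.3, +6 at 0.5 and +19 at 0.7. These figures rest on the plan's SD and correlation, on 0.5 being the SD of a score, and on assumed values of r.

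Two stronger readings are not supported. One is that power is lost whatever r is; the sign reverses at low r. The other is that the shortfall from 80% to 73% belongs to this point; it comes from using a t reference with 10 df instead of the normal approximation and is a separate matter.

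**What to change.** In Data analysis and statistics:

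1. Define the primary effect as the between-arm difference in NOSACQ-50 at follow-up, adjusted for the T0 score.
2. Add T0 NOSACQ-50 to the model as the care unit's T0 mean, plus the individual's deviation from it where that person has a T0 answer. The unit mean is available for workers who join later.
3. Treat the 14 patient-handling questions the same way, since Table 1 lists them under the primary outcome.
4. Reword the 0.7 in the power statement as a between-arm difference, and say what the SD of 0.5 is the SD of.

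A model with T0, T1 and T2 as outcomes and a common T0 mean is an alternative only if T0 answers are not influenced by allocation. The Procedure section places randomisation before baseline, so this cannot be taken for granted. Covariate adjustment would also be disturbed if knowledge of the arm shifted T0 answers. T0 response and scores should therefore be shown by arm, with the unadjusted estimate kept as a sensitivity analysis.

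The cost is a change of wording and one between-unit degree of freedom (10 to 9). The worst case in the range examined is a loss of about 5 points of power, if T0 and follow-up unit means are uncorrelated. No new data are needed.
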